##### Present Moment Awareness Ratings Scale

The PMARS is a 5-item questionnaire developed specifically for use in this study. Participants will be asked to rate their level of awareness of different aspects of present moment experiences. The PMARS was used in a previous pilot study ([name], MA, unpublished data, June 2017), and statistical analyses of its psychometric properties is underway [45].

##### Mind-Wandering Inventory

The MWI is a 5-point Likert-based questionnaire developed by the authors with items retroactively assessing the frequency of different types of mind-wandering events the respondent experienced during the mindful breathing task. The MWI was used in a previous pilot study ([name], MA, unpublished data, June 2017), and statistical analyses of its psychometric properties is underway [46].

##### Toronto Mindfulness Scale

The TMS is a state measure of mindfulness with 2 factors: curiosity and decentering. The TMS defines curiosity as an awareness of present moment experience with a curious attitude. Decentering is defined as an awareness qualified by distance and separation from current experience. The TMS has good internal consistency of alpha=.95. Current research demonstrates that the TMS is a reliable and valid measure of mindfulness that accurately measures curiosity and decentering [47].

##### Five-Factor Mindfulness Scale

The Five-Factor Mindfulness Scale (FFMS) is a 39-item Likert-based scale that assesses 5 aspects of mindfulness: nonreactivity to inner experience, acting with awareness, describing, nonjudging of inner experience, and observing. Research has demonstrated the FFMS to be valid in community and student samples with an internal consistency of alpha greater than .90 [48].

##### Socially Desirable Response Set 5-Item Survey

The Socially Desirable Response Set 5-Item Survey (SDRS-5) is a self-report measure designed to assess the tendency for individuals to provide socially desirable responses to self-reports of attitudes, behaviors, and feelings. Alpha reliability estimates for this instrument have been found to be between .66 and .68 [49].

##### Subjective Units of Distress Scale

The SUDS is a means of rating the severity of current distress (or anxiety), allowing for the monitoring of changes over time, where 0 is feeling perfectly relaxed and 100 is the worst anxiety and stress imaginable [50]. Participants will be asked to provide 0 to 100 SUDS ratings at baseline, post-stress induction, and after the post-stress meditation phases. The SUDS ratings will be used to do a manipulation check with respect to the mental arithmetic stressor and to monitor changes in stress over time.

### Statistical Analyses of Outcomes

This study has 2 coprimary hypotheses based on published recommendations for HRV analyses [31,39]. Generally, within-subject designs and analyses are preferred considering the high interindividual variations observed in HRV measures. To analyze differences in HRV with respect to MMA+ and MMA− between groups, change scores from stress to MM will be computed by subtracting stress-HRV from MM-HRV and used as the dependent variable in hypothesis 1a. In addition, within-subject changes in HRV according to the MM conditions and groups will be examined in hypothesis 1b. Results will be interpreted using significance values, confidence intervals, and effect sizes [51]. Intention-to-treat methodology will be the guiding principle of analyses. A complete case analysis approach will be used in anticipation of missing or unusable data.

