**Methods:**

This study is a two-arm randomized controlled trial (RCT) recruiting through a Web-based research participation pool at York University in Toronto, Canada. We are aiming for minimum 60 participants in each of CP, DA, and CF groups. Upon arriving to the laboratory, participants will be prescreened for classification into groups of CP, DA, or CF. Groups will be randomly assigned by a 1:1 ratio to an MMA (MMA+) condition or MM condition without the app (MMA−) after a brief stress induction procedure. In MMA+, participants will practice mindful breathing with a smartphone and press breath or other buttons at the sound of audio tones if their awareness was on breathing or another experience, respectively. HRV and respiration data will be obtained during rest (5 min), stress induction (5 min), and meditation conditions (12 min). Participants will complete psychological self-report inventories before and after the stress induction and after the meditation condition. Separate linear mixed models will be used to examine HRV and self-report inventories comparing groups and treatment conditions.

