### Primary End Point

#### Hypothesis 1a

HRV change scores during MM will be significantly higher in the CP and DA groups receiving MMA+ compared with corresponding CP and DA groups receiving MMA−, and will not differ between CF groups receiving MMA+ or MMA−.

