##### Stress Induction Phase

Following the baseline phase, a 5-min stress induction procedure will be performed whereby the participant engages in a set of mental arithmetic tasks, with the instruction to work as quickly as possible for maximal performance. Mental arithmetic was chosen as a stressor task because of its superior properties in eliciting sympathetic responses compared with other laboratory-based stressors [36].

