### Measures

#### Heart Rate Variability

There are several metrics that quantify HRV, the majority of which are either time based or frequency based. With the beat-to-beat interval series (also referred to as the R-R series), one can estimate the square root of the mean of squared successive differences between interbeat intervals (IBI), which has been found to be strongly correlated with respiration-based heart rate (HR) changes) [37]. It is important to note that both the IBI and the standard deviation of IBI’s are subject to increases with longer ECG recordings (influenced by slower, long-range fluctuations in HR independent of respiration-induced beat-to-beat changes). Thus, the Task Force [38] has recommended 5 min as a standardized length of HRV assessment in clinical and psychophysiological research. Using the frequency domain measure, one can examine the extent to which the HR varies within specific frequency ranges. The Fourier transform method deconstructs the time domain representation of the R-R series and computes a measure of *power* in several frequency bands in units of milliseconds squared (ms^2^). These bands include ultralow frequency (<0.04 Hz), low frequency (0.04-0.15 Hz), and high frequency (HF; 0.15-0.4 Hz). Typically, the frequency band of interest for the purposes of HRV interpretation is the HF band, as this is where the respiratory-linked beat-to-beat changes are reflected [37,39]. Although this is not intended to be an exhaustive account of HRV metrics, the aforementioned measures are the most commonly used in studies of vagal influence on cardiac chronotropy. On the basis of the recommendations by the 2 international committees [38,40], this study focuses on the frequency measure as the primary measure to interpret changes in vagal-mediated HRV across different conditions.

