#### Hypothesis 1a

To analyze HRV change in groups between the stress and MM phases, a linear mixed model will be used with group (CP, DA, and C) and condition (MMA+ and MMA−), with HRV change scores from stress to MM phases as the dependent variable. Planned comparisons will be computed comparing the MMA+ and MMA− conditions for each group (CP, DA, and C).

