#### Hypothesis 1b

To analyze HRV differences between groups and across phases, a 3-way linear mixed-effects ANOVA will be used with group (CP, DA, and C), phase (baseline, stress, and MM), and condition (MMA− and MMA+), with HRV as the dependent variable. Significant interactions will be followed up with simple effects analyses comparing the stress and MM phases for each group (CP, DA, C) within the 2 conditions (MMA+ and MMA−).

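### Coprimary H1b is followed up by within-arm stress-versus-meditation tests, which cannot separate an effect of meditation or the app from the end of the stressor

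*Protocol article*

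**What the plan says.** All references are to the protocol article.

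- **Outcome.** Statistical Analyses of Outcomes names two coprimary hypotheses. For H1a, "change scores from stress to MM will be computed by subtracting stress-HRV from MM-HRV".
- **H1a.** Under Primary End Point the claim is set against the arm without the app: "HRV change scores during MM will be significantly higher in the CP and DA groups receiving MMA+ compared with corresponding CP and DA groups receiving" the control condition. The analysis section matches it: "Planned comparisons will be computed comparing the MMA+ and MMA− conditions for each group (CP, DA, and C").
- **H1b.** Under Primary End Point this too is a comparison with MMA−: the rise from stress to meditation is to be greater in CP and DA participants using the app. The analysis is a group by phase by condition mixed model with baseline, stress and meditation as phases. Significant interactions lead to "simple effects analyses comparing the stress and MM phases for each group", carried out separately within MMA+ and within MMA−.
- **Phases.** "HRV and respiration data will be obtained during rest (5 min), stress induction (5 min), and meditation conditions (12 min"). In the stress phase, "a 5-min stress induction procedure will be performed whereby the participant engages in a set of mental arithmetic tasks". The only rest is the baseline before the stressor (Rest Phase). Both arms then practise mindful breathing for 12 min, seated with eyes closed (Intervention Arm, Control Arm).
- **Earlier work.** Principal Findings describes two previous studies by the team, each of which had a post-stress rest or audio-lecture condition beside meditation.

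**The concern.** Every participant moves from speeded arithmetic to sitting quietly with eyes closed. HRV should rise across that step whether or not meditation or the app does anything. A stress-versus-meditation test inside one arm therefore mixes recovery from the task with any effect of the practice, and this design has no post-stress rest condition to separate them.

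Two wrong conclusions become easy.

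1. A significant rise in an arm is read as vagal activation by meditation. If the arms do not differ, the planned follow-ups cannot tell whether both forms of meditation worked or everyone recovered from arithmetic.
2. A rise that is significant in MMA+ but not in MMA− is read as an app effect, although no test of the difference between the arms has been made in that step.

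The model already contains the seated, eyes-closed rest phase, but no planned follow-up uses it.

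**Working it through.** **1. The plan's own figure.** The sample size of 141 reproduces. For a 3-group by 3-phase interaction, λ = f²·N·m/(1−ρ) = 0.15² × 141 × 3 / 0.50 = 19.04, with df 4 and 2 × (141 − 3) = 276. At alpha 0.05 this gives power 0.952. The present point concerns what each contrast estimates and does not depend on this number.

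**2. What each contrast estimates.** Let D be the fall in HRV from rest to stress, R the part regained because the stressor ended, M the effect of mindful breathing common to both arms, and A the added effect of the app.

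| Contrast | Expected value |
|---|---|
| MM − stress within MMA+ | R + M + A |
| MM − stress within MMA− | R + M |
| MMA+ minus MMA− in (MM − stress) | A |
| MM − rest within MMA+ | (R − D) + M + A |
| MM − rest within MMA− | (R − D) + M |
| MMA+ minus MMA− in (MM − rest) | A |

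H1a estimates the third row. The H1b follow-ups test the first two rows, each against zero, and R is in both.

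**3. Size.** Inputs: 30 per arm within a group (Design section); change-score SD of 1 and rebound R of 0 to 1 SD (assumptions, since the article gives neither); M = 0; 20,000 simulated trials per setting; t-tests at two-sided 0.05.

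| R (SD) | Within MMA+, A = 0 | Within MMA−, A = 0 | Between arms, A = 0 | Between arms, A = 0.5 SD |
|---|---|---|---|---|
| 0 | 5.1% | 4.9% | 4.8% | 47.9% |
| 0.25 | 26.3% | 26.7% | 4.9% | 47.7% |
| 0.5 | 75.1% | 75.6% | 4.7% | 47.7% |
| 0.75 | 97.9% | 97.9% | 5.1% | 47.8% |
| 1.0 | 100% | 100% | 4.5% | 48.3% |

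With A = 0.5 the between-arm estimate is 0.50 at every R. The rebound changes neither the error rate nor the estimate of the randomised comparison. It drives the within-arm tests.

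**4. Significant in one arm only.** The arms are independent, so with no app effect the chance in a given group that MMA+ is significant and MMA− is not is the product of the two rates:

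- R = 0.25: 0.263 × (1 − 0.267) = 0.19
- R = 0.5: 0.751 × (1 − 0.756) = 0.18
- R = 0.75: 0.979 × (1 − 0.979) = 0.02

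These are rates once the follow-ups are run. They do not include the chance that a significant interaction opens them.

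**The case against.** **The coprimary hypotheses are randomised comparisons.** This stands in full for H1a. Both arms share the stressor, posture and nominal 12-min task, so common recovery cancels, as the tables show. A reader might infer that the primary change score only measures the end of the stressor and is invalid without a rest arm. The documents do not support that: the stated question is what the app adds to mindful breathing, and a rest arm would answer a different one.

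**The simple effects follow only significant interactions.** This limits how often they are run. But the plan does not say which interaction opens them. A group-by-phase interaction alone would do so, and Principal Findings anticipates different HRV patterns in clinical groups. Even after a significant condition-by-phase term, a within-arm test does not show in which group the arms differ.

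**Recording length.** A reader might infer that comparing 5 min with 12 min biases the outcome, since the Heart Rate Variability section notes that a task force has "recommended 5 min as a standardized length of HRV assessment in clinical and psychophysiological research". That section ties length sensitivity to interbeat-interval indices, whereas HF-HRV is primary. Nothing says that the 12 min are scored as one value, and epoching is commonly left to a fuller plan. The app schedule sums to 4 × (5+15+25+35+45+55) = 720 s of silence, or 744 s if the 24 one-second tones are added, a trivial difference from 12 min.

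**Rest before stress is an imperfect reference.** True. Order and residual stress affect it, and between arms it has the same expectation as the stress reference. It helps only in reading the within-arm change.

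**Post-stress recovery is itself of interest here.** Also true: Background and Principal Findings treat vagal recovery as part of the construct. Counting only HRV above rest as vagal activation, or scoring only the late minutes as primary, would be a debatable redefinition with 189 participants already recruited.

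**Conclusion.** The concern holds for the H1b follow-ups and not for H1a. The within-condition tests do not test what H1b claims, and with no effect of meditation or app they reject in 26% to 98% of simulated trials for rebounds of 0.25 to 0.75 SD. That range rests on an assumed rebound and SD, a normal model and 30 per arm. The direction does not: any positive recovery pushes the within-arm tests towards significance. The between-arm comparison is unaffected.

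The trial's primary test is therefore not undermined. What needs correcting is the route by which a coprimary result could be misread. It is worth changing because the article itself fixes these follow-ups, and the data for a better reading are already being recorded.

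**What to change.** In Statistical Analyses of Outcomes, Hypothesis 1b:

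1. Base inference on the condition-by-phase contrast, MMA+ minus MMA− in the stress-to-meditation change, within each of CP, DA and CF. With complete cases and no covariate its point estimate equals that of H1a, so the two coprimary analyses will agree on the app effect.
2. Add a meditation-minus-rest contrast by arm, from the 5-min seated, eyes-closed baseline already in the model, and state that pre-stress rest is an imperfect reference because of order and residual stress.
3. State that a within-arm stress-to-meditation rise alone will be reported as change after the stressor, not as an effect of meditation or the app, and that significance in one arm but not the other will not be read as a difference.
4. Optionally, add a 5-min meditation epoch matched to the other phases as a sensitivity analysis. It should not replace the primary window.

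The cost is one extra contrast on recordings already being made, some re-segmentation if the optional epoch is used, and a more modest reading of within-arm rises. No new data and no change to the H1a outcome are needed.

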### Sample Size Estimation

Sample size estimate for a repeated-measures linear mixed-effects analysis of variance (ANOVA) with 3 groups (CP, DA, and CF), 2 conditions (MMA+, MMA−), and 3 phases (baseline, stress induction, and MM) indicates that a total of 141 participants are needed to detect small-to-medium effect size (f=0.15) HRV changes with a type I error rate (alpha) of .05, a power of 0.95, and a 0.50 correlation between repeated measures (G*Power; Heinrich Heine University Düsseldorf). The small-to-medium effect size corresponds to previously published studies of HRV increases during brief mindfulness practice [13,14]. Recruitment of more than 180 participants will allow for an attrition rate of approximately 20% because of withdrawals, dropouts, technical failures, and missing data. On the basis of prescreening and recruitment numbers in our past pilot study ([name], MA, unpublished data, June 2017), we found the percentage of participants reporting diagnosed CP, severe depression, or anxiety symptoms to be 27%, 33%, and 41%, respectively. Accordingly, the combined number of students expected to be prescreened for eligibility to enroll 60 participants per group will be approximately N=550.

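### Hypothesis 1a analyses an unadjusted MM-minus-stress change score: a valid test, but it gives up precision that the recorded stress and rest HRV could supply

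*Protocol article*

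**What the plan says.** Under Statistical Analyses of Outcomes the protocol says that "change scores from stress to MM will be computed by subtracting stress-HRV from MM-HRV and used as the dependent variable in hypothesis 1a". Its subsection Hypothesis 1a repeats the choice, "with HRV change scores from stress to MM phases as the dependent variable", and lists group (CP, DA, condition-free) and condition (MMA+, MMA−) as the model terms. Planned comparisons of MMA+ with MMA− follow within each group. No HRV measurement is named as a covariate.

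HRV is recorded in three phases: rest, stress and MM (Experimental Session; Heart Rate Variability). Rest HRV does not enter hypothesis 1a. In hypothesis 1b it appears as one level of the phase factor, and the follow-up contrasts there again compare stress with MM. The only covariate named for the HRV analyses is respiration rate, to be used if it differs between phases or groups (Respiration Rate).

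Sample Size Estimation assumes "a type I error rate (alpha) of .05, a power of 0.95, and a 0.50 correlation between repeated measures".

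**The concern.** Subtracting stress HRV amounts to regressing MM-phase HRV on stress HRV with the slope forced to 1. With equal variances and a correlation of 0.50, the least-squares slope is 0.50, so subtraction removes too much. A participant with high stress HRV is then expected to show a smaller change whatever the condition. That predictable variation stays in the error term.

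Rest HRV carries further information about a participant's usual level, and hypothesis 1a does not use it.

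The comparisons affected are the small ones. Each within-group contrast has 30 participants per arm as planned, or about 24 after the allowed 20% attrition (30 × 0.80). Results reports only 41 CP participants by July 2019, and CP is one of the two groups in which hypothesis 1a predicts an effect.

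**Working it through.** **Inputs from the protocol.** Correlation 0.50, alpha 0.05, f = 0.15, three groups, three phases, stated total 141 (Sample Size Estimation); 30 per arm per group (Design).

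**Assumptions, because no SDs or phase-specific correlations are given.** Equal variance in each phase (set to 1) and one common correlation ρ between any two phases.

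**1. The plan's own figure.** For a repeated-measures group-by-phase interaction, λ = f²·N·m/(1−ρ). With N = 141 and m = 3, λ = 0.0225 × 141 × 3 / 0.50 = 19.04, on (3−1)(3−1) = 4 and (141−3)(3−1) = 276 df. Power is 0.952. The smallest N reaching 0.95 is 140, or 141 in equal groups, so the stated 141 reproduces and 0.50 is the working correlation. This calculation does not size the within-group MMA+ versus MMA− contrasts of hypothesis 1a.

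**2. Residual variance of the hypothesis 1a outcome.**
- Change score: 2(1−ρ) = 2 × 0.50 = 1.00
- MM adjusted for stress: 1−ρ² = 1 − 0.25 = 0.75
- MM adjusted for stress and rest: 1 − 2ρ²/(1+ρ) = 1 − 0.50/1.50 = 0.667

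A simulation of 1,000,000 draws gave 1.000, 0.750 and 0.667. The proportional cuts simplify to (1−ρ)/2 for stress alone and 1/[2(1+ρ)] for both. In sample-size terms the change score needs 1/0.75 = 1.33 or 1/0.667 = 1.50 times as many participants for the same precision.

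**3. Sensitivity to ρ.**

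| ρ | Change | Stress | Stress + rest | Cut, stress | Cut, both |
|---|---|---|---|---|---|
| 0.3 | 1.40 | 0.91 | 0.862 | 35% | 38% |
| 0.5 | 1.00 | 0.75 | 0.667 | 25% | 33% |
| 0.6 | 0.80 | 0.64 | 0.550 | 20% | 31% |
| 0.7 | 0.60 | 0.51 | 0.424 | 15% | 29% |
| 0.8 | 0.40 | 0.36 | 0.289 | 10% | 28% |
| 0.9 | 0.20 | 0.19 | 0.147 | 5% | 26% |

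**4. Which covariate does the work.** Adding rest HRV alone to the change-score model gains nothing under this structure. The covariance of (MM − stress) with rest is ρ − ρ = 0, and simulation confirmed a residual of 1.00. The gain comes from freeing the slope on stress HRV; rest HRV then adds to it.

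**5. Illustration in power.** The protocol gives no within-group effect in SD units. For an assumed difference of 0.5 SD (single-phase SD, ρ = 0.50, two-sided 0.05), power for one within-group contrast is:

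| Per arm | Change | Stress | Stress + rest |
|---|---|---|---|
| 30 | 0.486 | 0.604 | 0.655 |
| 24 | 0.405 | 0.510 | 0.558 |

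The number per arm for 80% power is 63, 48 and 42 respectively. At an assumed 0.3 SD and 30 per arm, power is 0.211, 0.266 and 0.293; at 0.75 SD it is 0.823, 0.916 and 0.943.

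**The case against.** The strongest reply is that the change score is a legitimate choice with a stated reason: the protocol prefers within-subject analysis because HRV varies so much between people. Condition is randomised within each group, so the contrast is unbiased and the test valid. All of that stands. A reader might infer from regression to the mean that the comparison is biased. It is not: chance imbalance in stress HRV averages out over randomisations and is already counted in the larger variance. The stated reason, however, supports adjustment at least as well as subtraction.

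Strong between-person variation could also mean a correlation above 0.50, where the gain from stress HRV alone shrinks to 10% at 0.8. That stands too, although the gain from both covariates stays above 25% throughout the table.

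Four further inferences go beyond the document:
- *Baseline HRV is ignored.* This is true of hypothesis 1a only. Hypothesis 1b is coprimary and includes rest as a phase, though it does not condition on it.
- *The outcome is analysed in raw ms².* The Heart Rate Variability section gives that unit when describing spectral power in general. The article does not fix the analysis scale, which may sit in a fuller document.
- *Calling the analysis a linear mixed model invalidates it.* With one change score per participant the label adds nothing, but it changes no result.
- *CP and DA should be pooled.* Hypothesis 1a specifies per-group comparisons, and the precision problem does not call for a new estimand.

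One objection bears on the remedy. Stress HRV is a safe covariate only if allocation cannot influence it. The Abstract and the end of the Background place randomisation after stress induction. Group Classification and Randomization has unblinded staff assign the arm after prescreening, and Post-Stress Meditation Phase refers to randomisation after the pre-study questionnaires. The 1-min app practice is placed before the intervention session, without saying whether it precedes the stress phase.

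**Conclusion.** The point holds as a loss of precision in a coprimary analysis, not as an invalid or biased test. At the plan's correlation of 0.50, the change score carries residual variance 1.00, against 0.75 with stress HRV as covariate (25% less) and 0.667 with stress and rest HRV (33% less). For correlations of 0.6 to 0.8 the reductions are 20% to 10% and 31% to 28%.

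These sizes rest on equal phase variances and a single common correlation, neither of which the protocol documents. With unequal variances the best slope on stress HRV is ρ times the ratio of the MM to the stress SD. If that product happened to equal 1, stress adjustment alone would gain nothing. A freely estimated slope cannot do worse than the fixed one beyond the cost of one or two degrees of freedom. The power figures are illustrations at assumed effects.

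This is an inexpensive improvement, most useful in the smaller clinical groups.

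**What to change.** Keep the planned MMA+ versus MMA− comparison in each of the three groups. Obtain it from a linear model with MM-phase HRV as the outcome, on whatever scale the plan uses, with group, condition and group-by-condition as factors and stress-phase and rest-phase HRV as covariates. Record the change as a dated amendment before HRV is analysed by condition. The unadjusted change score can be reported as a sensitivity analysis.

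First, reconcile the passages on the timing of allocation, and state when participants learn their condition and do the 1-min app practice. If both happen only after the stress phase, use both covariates. If either can precede it, stress HRV may respond to allocation and should be neither subtracted nor adjusted for. In that case use MM-phase HRV adjusted for rest HRV alone. Under the same assumptions this gives 1 − 0.50² = 0.75, still 25% below the change score. The protocol should also confirm that neither happens before the rest recording.

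The cost is wording, one clarification of procedure and at most two degrees of freedom. All three HRV measurements are already collected. With 189 participants recruited by July 2019, the practical constraint is to fix the change before results by condition are seen.
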